## Abstract

INTRICATE is a prospective double-blind placebo-controlled feasibility study, assessing the influence of combined vitamin K2 and vitamin D3 supplementation on micro-calcification in carotid artery disease as imaged by hybrid Sodium [^18^F]Fluoride (Na[^18^F]F) positron emission tomography (PET)/ magnetic resonance imaging (MRI). Arterial calcification is an actively regulated process and results from the imbalance between calcification promoting and inhibiting factors. Considering the recent advancements in medical imaging, ultrasound (US), PET/MRI, and computed tomography (CT) can be used for the selection and stratification of patients with atherosclerosis. Fifty-two subjects with asymptomatic carotid artery disease on at least one side of the neck will be included in the study. At baseline, an Na[^18^F]F PET/MRI and CT examination will be performed. Afterwards, subjects will be randomized (1:1) to a vitamin K (400 µg MK-7/day) and vitamin D3 (80 µg/day) or to placebo. At the 3-month follow-up, subjects will undergo a second Na[^18^F]F PET/MRI and CT scan. The primary endpoint is the change in Na[^18^F]F PET/MRI (baseline vs. after 3 months) in the treatment group as compared to the placebo arm. Secondary endpoints are changes in plaque composition and in blood-biomarkers. The INTRICATE trial bears the potential to open novel avenues for future large scale randomized controlled trials to intervene in the plaque development and micro-calcification progression.

## 1. Introduction

Arterial calcification is an active process and results from the imbalance between calcification promoting and inhibiting factors [1]. Extracellular matrix calcification is initiated by matrix vesicles, secreted by osteoblasts or osteoblast-like cells (i.e., vascular smooth muscle cells that acquired the pathological osteogenic phenotype [2]), inducing the nucleation of calcium phosphate crystals (i.e., hydroxyapatite) [3]. Accumulation of calcium and phosphate ions into vesicles will initiate crystal formation [3]. Next, hydroxyapatite crystals will elongate radially, penetrate the vesicle membrane, and will form calcifying nodules with neighboring matrix vesicles [3]. The subsequent growth of the calcifying nodule seems to be regulated by the availability of organic compounds (e.g., matrix Gla protein, MGP) [3].

Considering the recent advancements in medical imaging, ultrasound (US), magnetic resonance imaging (MRI), computed tomography (CT), as well as positron emission tomography (PET) with different (new) PET-tracers can be used for the selection and stratification of patients with atherosclerosis [4,5,6,7]. In a recent review, the superiority of sodium [^18^F]Fluoride (Na[^18^F]F) PET over other modalities to correctly identify micro-calcified plaques has been elaborated [8]. Na[^18^F]F PET is considered to be the only available clinical tool that can non-invasively detect (potentially) vulnerable micro-calcified plaques more sensitively than CT [8,9].

In the last two decades, a series of proteins that can bind calcium ions have been discovered and most of them share a common feature, the γ-carboxyglutamic acid (Gla) rich domain. As a result that Gla-residues are biologically converted from protein-bound glutamic acid residues by an enzyme which uses vitamin K as a cofactor, all these proteins are called vitamin K dependent proteins. MGP [10] is one of the most studied vitamin K dependent proteins that has proven to have a role in the protection against ectopic calcification [11,12].

MGP is able to avidly bind the calcium from hydroxyapatite crystals [13] and therefore to block the growth of calcifying nodules. In order to become biologically active, MGP requires two post-translational modifications: γ-carboxylation and phosphorylation.

MGP can be found in the blood stream and there are numerous human and animal studies in which MGP has been used as a marker for different inflammatory diseases that also involve calcification (e.g., coronary artery disease, type 2 diabetes, chronic kidney disease) [14,15,16]. High plasma levels of dephosphorylated uncarboxylated MGP (dp-ucMGP) correlate with an increased cardiovascular risk in type 2 diabetes patients [17]. Moreover, dp-ucMGP inversely correlates with vascular calcification levels of patients suffering from coronary artery disease [18], type 2 diabetes [19], and end stage kidney disease [20]. One study did not measure the inactive form, but the total concentration of MGP and found a significant reduction in MGP synthesis in patients with aortic valve calcification [21] and chronic kidney disease [22]. Moreover, low plasma levels of dp-ucMGP are associated with an increased all-cause and cardiovascular mortality in the general European population [23].

Therefore, dp-ucMGP might be used as a marker for vitamin K status and in extension for vascular health.

In a recent review paper, we have presented emerging data, which suggests vitamin K—especially Menaquinone-7 (MK-7)—as a cost-effective method of delaying progression of vascular calcification [8]. Although these studies support the idea that MK-7 protects against vascular calcification, there have been no controlled trials in humans assessing the effects of MK-7 supplementation on arterial calcification in the context of atherosclerosis.

## 2. Study Design

The INTRICATE trial (acronym for the “Effects of combined vitamin K2 and vitamin D3 supplementation on Na[^18^F]F PET/MRI in patients with carotid artery disease” trial) is a double-blind randomized, placebo-controlled feasibility study, performed at the Maastricht University Medical Center, with an end of the study visit after 3 months. The research file of this trial, including the study protocol, was approved by the accredited local Medical Ethics Committee of the Academic Hospital Maastricht and University of Maastricht in the Netherlands (i.e., METC azM/UM) under the file number NL69450.068.19/METC300103 and is being conducted according to the principles of the Declaration of Helsinki. The INTRICATE trial is also registered at clinicaltrials.gov under NCT04010578. All subjects give their written informed consent for inclusion before they participate in the study. The informed consent is being received in writing, in the native language of the subjects (i.e., Dutch) and is available in the Supplementary Materials.

Subjects with asymptomatic carotid artery disease (i.e., on the common or the internal carotid) on at least one side with a degree of stenosis > 25% (according to ECST criteria) as detected by means of B-mode US and who meet the inclusion criteria will be recruited. After providing informed consent, they will be randomized in two groups:the first group will receive a daily dose of 400 µg MK-7 and 80 µg D3 andthe second (i.e., control) group will receive a placebo.

Both, the investigators as well as the patients will be blinded regarding the treatment used.

At baseline, a Na[^18^F]F PET/MRI, a CAC scan, and an US examination of the neck vessels will be performed; moreover, samples of venous blood will be taken. Subjects will be asked for a follow-up evaluation after 3 months of supplementation, when Na[^18^F]F PET/MRI, CAC scan, and US scan will be repeated, in order to measure the degree of vascular calcifications and the changes in time of atherosclerosis. Additionally, venous blood samples will be obtained by standard venous puncture for routine biochemical, hematological, and serum biomarker assessments.

## 3. Study Population

Patients with asymptomatic carotid artery disease on one side, who meet the inclusion criteria and who provide a signed informed consent are being invited in this study.

### 3.1. Inclusion Criteria

In order to be eligible to participate in this study, a subject must meet all following criteria:Asymptomatic carotid artery disease on at least one side with a degree of stenosis > 25% (according to the ECST criteria). If the patient has a symptomatic carotid artery disease on the contra-lateral side, he/she will still be included in the study, if intensified medical treatment for this symptomatic stenosis (e.g., statins, antiplatelet medication) was started ≥6 month before inclusion of the patient. This protocol was chosen in order to assure a stable situation on the plaque(s), which avoids an overspill from this medication on the assumed effects of the supplementation.Age older than 18 years.Signed informed consent provided.

### 3.2. Exclusion Criteria

A potential subject who meets any of the following criteria will be excluded from participation in this study:Antiplatelet or cholesterol lowering medication started within the past 6 months.Chronic or paroxysmal atrial fibrillation.Already performed or scheduled coronary or carotid revascularization procedure (e.g., stent implantation, coronary artery bypass graft, balloon-dilatation, endarterectomy, angioplasty).History of myocardial infarction or stroke.Malignant disease (except for treated basal-cell or squamous cell carcinoma).Use of vitamin K antagonists treatment.A life-expectancy < 1 year.Claustrophobia.Presence of a pacemaker, intra-cardiac defibrillator, or metallic implant (e.g., vascular clip, neuro-stimulator, cochlear implant, metal splinter in the eye).Body weight > 130 kg or body habitus that does not fit into the gantry.Pregnancy or wish to become pregnant in the near future.Breast feeding.(History of) metabolic or gastrointestinal disease.Use of vitamin K or D containing supplements or vitamin K-rich foods (e.g., fermented soya).Chronic inflammatory disease.Systemic treatment or topical treatment likely to interfere with evaluation of the study parameters.Corticoid treatment.Participation in a clinical study within one month before enrolment in the current study.

## 4. Study Objectives and Statistical Analyses Plan

The objective of this study is to assess the influence of MK-7 and vitamin D3 on the pathophysiological process of arterial micro-calcification in carotid artery disease as assessed by hybrid Na[^18^F]F PET/MRI. Furthermore, the longitudinal change of micro-calcifications and plaque composition and volume under this supplementation in coronary artery disease patients will be assessed by means of MRI and CAC scan. The aforementioned scans will be compared between baseline and the end of the study visit in a group receiving vitamin K supplementation as compared to the placebo group. In addition, dp-ucMGP will be measured, in order to determine whether this biomarker can be used to assess the degree of calcification in the arterial wall of patients with coronary and carotid artery disease. Finally, blood samples will be stored in the Biobank, creating the opportunity to investigate new biomarkers regarding vitamins K and D status in the future (e.g., their influence on osteocalcin or alkaline phosphatase).

### 4.1. Primary Objective

We investigated whether MK-7 and vitamin D3 supplementation can diminish, halt, or even reverse the development of arterial micro-calcification in the carotid arteries in the context of atherosclerosis as detected by Na[^18^F]F PET/MRI compared to placebo after 3 months.

### 4.2. Secondary Objectives

Secondary objectives of the trial include assessing whether:the vitamin supplementation can diminish, halt, or even reverse the development of arterial micro-calcification in the coronary arteries in the context of atherosclerosis as detected by CAC score compared to placebo after 3 months;the primary parameter correlates or is able to predict the results of the CAC score;the vitamin supplementation can influence MRI parameters such as normalized wall index (i.e., measurement of plaque burden), intra-plaque hemorrhage volume, lipid-rich necrotic core volume, and fibrous cap status;the vitamin supplementation can influence US after 3 months of supplementation;Na[^18^F]F uptake in the carotids is associated with US at the end of the study visit;the vitamin supplementation is influencing plasma levels of dp-ucMGP after 3 months, in comparison with a placebo, in order to select a possible peripheral marker for vitamin K-status;baseline plasma levels of dp-ucMGP can be reliable biomarkers of plaque vulnerability and of its calcified state;there is a correlation between serum MK-7 concentrations and the values of the prothrombin time (PT) or the international normalized ratio (INR).

### 4.3. Statistical Analyses Plan

Our null hypotheses states that MK-7 and vitamin D3 do not influence the change (i.e., progression) of micro-calcifications in 3 months of supplementation when compared to a placebo; there will be no difference in the degree of calcification between the MK7+D3 group vs. the placebo at the end of the study. Our alternative hypothesis states that MK-7 and vitamin D3 have a greater effect on the change of micro-calcification in 3 months of supplementation compared to placebo.

The descriptive statistics for each variable at baseline will be presented for both groups combined and individually (i.e., MK7+D3 and placebo) for each of the following parameters: mean, standard deviation of the variable, standard error of the mean, range (minimum-maximum), median, quartiles, and confidence intervals where necessary. Descriptive statistics for variables at the end of the study will be presented separate for both groups (i.e., MK7+D3 and placebo).

Both intention-to-treat and per protocol analysis will be performed. For the intention-to-treat analysis, all randomized subjects (with data available from the end of the study visit) will be included. In the per protocol analysis, only subjects who fully complied with the prescribed supplementation will be included.

The main outcome parameter (i.e., the longitudinal change time of micro-calcification as measured by the Na[^18^F]F uptake via hybrid PET/MRI) will be presented as a continuous variable. It will be expressed as a mean difference (i.e., the standard uptake value and target-to-background radio of Na[^18^F]F at the end of the study visit minus Na[^18^F]F maximal uptake at baseline). To investigate the existence of significant predictor(s) for the main outcome parameter (i.e., the longitudinal change of micro-calcification), univariate analysis will be used. If the significance level (i.e., α) will be between 5% and 25% at the univariate *t*-test hypothesis testing (i.e., *p* > 0.05 and *p* < 0.25), a multivariate analysis will be used, in order to investigate a possible association or interaction between variables.

In order to decide to either reject or accept our null hypothesis, a two-sided confidence interval using 95% confidence will be calculated and reported. A two-sided hypothesis test using a significance level (i.e., α) of 5% will also be reported.

The CAC score and the US data will be presented as continuous variables. Their longitudinal change will be also expressed as a mean difference (i.e., value at the end of the study visit minus value at baseline) and will be presented as continuous variables.

For the continuous data including age, blood pressure, body-mass index, lipid-rich necrotic volume, normalized wall index, dp-ucMGP, and other laboratory tests, the distribution of variables will be analyzed (verification of normality of distribution for all subjects) by histograms. To investigate the existence of significant predictor(s) for the secondary outcome parameters, univariate analysis will be used. If the significance level (i.e., α) will be between 5% and 25% at the univariate t-test hypothesis testing (i.e., *p* > 0.05 and *p* < 0.25), a multivariate analysis will be used, in order to investigate a possible association or interaction between variables. If variables display no normal distribution, data will be transformed using appropriate transformations. If transformation is not possible, this data is analyzed by non-parametric statistical tests (i.e., Chi-square test).

Baseline parameters will be presented: sex, age, bodyweight, length, body-mass index, medical history, medication, family history, and cardiovascular risk factors.

Health status and use/changes of medication will be verified during the baseline visit and at the end of the study visit.

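### The set labelled intention-to-treat is an available-case set, and the plan does not say whether it or the per-protocol analysis decides the null hypothesis

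*Protocol article*

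**What the plan says.** Section 4.3 of the protocol article announces two analyses: "Both intention-to-treat and per protocol analysis will be performed". For the one called intention-to-treat, "all randomized subjects (with data available from the end of the study visit) will be included". For the per-protocol one, "only subjects who fully complied with the prescribed supplementation will be included".

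Of the main outcome, the change in tracer uptake on PET/MRI, the same section says "It will be expressed as a mean difference", taken as the end-of-study value minus the baseline value. Section 2 provides for a single later assessment: "Subjects will be asked for a follow-up evaluation after 3 months of supplementation". Table 1 agrees, with one baseline column and one end-of-study column for PET/MRI.

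For the decision on the null hypothesis, section 4.3 refers to one two-sided 95% confidence interval and adds: "A two-sided hypothesis test using a significance level (i.e., α) of 5% will also be reported". It does not say from which of the two analysis sets the interval and the test are taken.

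**The concern.** An intention-to-treat set is fixed at randomisation. The set defined here also depends on whether end-of-study data exist, which is known only afterwards. If the reasons for missing data differ by arm, or relate to health in a way that also affects uptake, the subjects left in the two arms are no longer comparable by virtue of randomisation. A report calling the result intention-to-treat would then claim a protection that the analysis does not have.

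The second problem is the decision rule. Two analysis sets give two intervals and two p-values, while the text speaks of one interval that settles the null hypothesis. If the two disagree, the article offers no agreed reading, and the choice could be made after the results are seen.

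**Working it through.** **What the definition amounts to.** The outcome is a difference between two scans, and there is one post-baseline visit. A subject without the second scan has no change score and no intermediate value to stand in for it. For the primary endpoint, the condition in the intention-to-treat definition therefore means having the second PET/MRI. Strictly, the text requires data from the end-of-study visit and does not mention a scan. For other endpoints, such as blood markers, a subject without the scan could still qualify.

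**Inputs from the article.** The Abstract gives the size, "Fifty-two subjects with asymptomatic carotid artery disease on at least one side of the neck will be included in the study", and the allocation, "subjects will be randomized (1:1" for active to placebo), so 26 per arm if balanced. Alpha is 5%, two-sided (section 4.3). The article states no power, effect size, SD or dropout rate, so it has no figure on this point to reproduce. All missingness shares and mean gaps below are assumptions.

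**Detectable difference with complete data.** Normal approximation at 80% power:

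(1.960 + 0.842) × √(2/26) = 2.802 × 0.277 = 0.78 SD.

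With the t distribution the figure is 0.79 SD.

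**Loss of precision if subjects drop out equally from both arms** (normal approximation):

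| Assumed missing | Subjects left of 52 | Detectable difference (SD) | Power at 0.78 SD |
|---|---|---|---|
| 0% | 52 | 0.78 | 80% |
| 5% | about 49 | 0.80 | 78% |
| 10% | about 47 | 0.82 | 76% |
| 15% | about 44 | 0.84 | 73% |
| 20% | about 42 | 0.87 | 71% |

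**Bias.** Let a share m of an arm be missing, and let their mean change differ from that of observed subjects by k SD. The mean over all randomised subjects in that arm is (1 − m) × observed mean + m × missing mean. The observed mean is therefore off by m × k. The bias in the contrast is the difference between the arms in m × k. It cancels if both arms lose the same share with the same gap, and it equals m × k if only one arm loses subjects:

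| m (one arm only) | k = 0.25 | k = 0.5 | k = 1 |
|---|---|---|---|
| 5% | 0.0125 | 0.025 | 0.05 |
| 10% | 0.025 | 0.05 | 0.10 |
| 20% | 0.05 | 0.10 | 0.20 |

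The range is about 0.01 to 0.20 SD. Against 0.78 SD, that is 0.0125/0.777 = 2% to 0.20/0.777 = 26% of the detectable difference.

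**Two analyses, one decision.** If each test held its 5% level and either could be cited as the answer, the chance of at least one false rejection would lie between 5% and 2 × 5% = 10%, depending on how far the two sets overlap. Naming one analysis as decisive removes the question.

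**The case against.** The restriction is printed inside the definition, so no reader of section 4.3 is misled about who is analysed. With one post-baseline visit, a subject who does not return cannot contribute a change score. Analysing the observed subjects in their randomised arms is valid if data are missing at random given what is modelled. Multiple imputation from baseline variables adds little to a baseline-adjusted analysis under that same assumption. Methods for missing data are commonly set out in an analysis plan or full protocol, neither of which is shown, and this is a small feasibility study.

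Most of that stands. The article is not at fault for leaving out imputation details. What remains is that it fixes a set, gives it a name that its definition contradicts, and leaves open which of two analyses decides.

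Some stronger readings are tempting, and the article does not support them:

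- A reader might infer that the per-protocol set also fails its name. It does not: restricting to subjects who complied is what per protocol means.
- A reader might take full compliance to mean that one missed day excludes a subject, leaving only a handful. The article gives no cut-off and lists only a drug count in Table 1. Under that literal reading, with 90 independent days, p^90 gives 16% of subjects at an assumed daily adherence of 98%, 40% at 99%, 64% at 99.5% and 91% at 99.9%. The result depends almost wholly on the assumption, and a cut-off may stand in a document not shown.
- A reader might infer that non-adherent subjects are not called back, or that serious adverse events or revascularisation will cause missed scans. Section 2 sets no adherence condition for the 3-month visit. Section 6 links serious adverse events to unblinding only, and section 3.2 lists revascularisation only as an entry exclusion.

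**Conclusion.** The point holds for the label and for the missing designation of a primary analysis. The set called intention-to-treat is an available-case set for the primary endpoint, and section 4.3 does not say whether it or the per-protocol set settles the null hypothesis.

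The likely effect is modest, and its true size cannot be known from the article. Under one-sided missingness of 5–20% and a gap of 0.25–1 SD, the bias is about 0.01–0.20 SD, against a detectable difference of 0.78–0.79 SD with 26 per arm. The upper end needs both heavy loss in a single arm and a large gap. With no missing second scans, the label would be accurate for the primary endpoint and only the question of which analysis decides would remain. The change is worth making because it is cheap and governs what the trial may claim.

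**What to change.** In section 4.3, or in the analysis plan before unblinding:

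1. Name the as-randomised analysis as primary, and state that its interval and test decide the null hypothesis.
2. Call its set available-case or modified intention-to-treat. State the missing-at-random assumption, and include baseline uptake and the stenosis stratum used at randomisation (section 6) in the model.
3. Add a sensitivity analysis of all randomised subjects: multiple imputation by arm, with a delta shift applied to imputed values over a prespecified range. The shift is the informative part, because imputation from baseline data alone largely repeats the primary assumption.
4. Report the number without a second scan, with reasons, by arm.
5. Label the per-protocol analysis as supportive, and define full compliance by a threshold on the drug count, fixed before unblinding and used for analysis only.

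The cost is a few sentences and a small amount of extra programming. Treatment, visits and sample size do not change.

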## 6. Randomization, Blinding, and Treatment Allocation

A custom-made software with minimization as a randomization method (i.e., operated by the researcher) will randomize consecutive patients in the two arms, using the carotid stenosis as a stratification factor. The software will stratify the subjects according to the initial carotid stenosis into one of the following groups: stenosis 25–50% or stenosis > 50%. This software will assign subjects with a specific randomization number. This randomization number will be used by NattoPharma (Oslo, Norway) for coding and labelling of the capsule bottles. The list with all the randomization number will be stored in a secure location and will not be accessible for the investigators during this study.

The study code will be de-blinded if a serious adverse event occurs in an individual subject.

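### The primary analysis rests on a change score without baseline uptake or the stenosis stratum as covariates, which gives up some precision at no saving.

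*Protocol article*

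**What the plan says.** All references are to the protocol article.

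- **Size and allocation (Abstract).** "Fifty-two subjects with asymptomatic carotid artery disease on at least one side of the neck will be included in the study", and "subjects will be randomized (1:1"), which gives 26 per arm.
- **Primary outcome (section 4.3).** It is a change over 3 months: "It will be expressed as a mean difference". The subtraction takes the standard uptake value and target-to-background ratio "at the end of the study visit minus Na[^18^F]F maximal uptake at baseline".
- **Analysis (section 4.3).** For predictors of the main outcome, "the longitudinal change of micro-calcification), univariate analysis will be used". The t-test is named in the next sentence. If its p-value lies between 0.05 and 0.25, a multivariate analysis follows, with no variables listed.
- **Decision rule (section 4.3).** A two-sided 95% confidence interval is used, and "A two-sided hypothesis test using a significance level (i.e., α) of 5% will also be reported".
- **Null hypothesis (section 4.3).** It is first stated as no influence on change, then as "there will be no difference in the degree of calcification between the MK7+D3 group vs. the placebo at the end of the study".
- **Randomisation (section 6).** Minimisation is carried out "using the carotid stenosis as a stratification factor", with levels 25–50% and > 50%. Section 4.3 does not mention stenosis.

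**The concern.** Every subject has a PET/MRI at baseline and another at 3 months, so baseline uptake is available to the analysis without further cost. Subtracting it fixes its coefficient at 1. When the correlation between visits is below 1, that over-corrects: measurement noise at baseline passes in full into the outcome. A regression coefficient estimated from the data avoids this.

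The stenosis stratum was important enough to balance by design, yet it is absent from the analysis described.

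What is at stake is the precision of the main estimate in a 52-subject trial and a single, unambiguous primary result. The conditional multivariate step does not settle either. Whether an adjusted result exists depends on the unadjusted p-value, and the adjustment set is left open.

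**Working it through.** **Inputs.** From the article: 52 subjects, 1:1, two-sided 5%, one baseline and one 3-month scan. The article gives no effect size, standard deviation, power or correlation, so it has no figure of its own to reproduce. The correlation rho and a starting power of 80% are assumptions. Using 26 per arm supposes that nobody is lost; the variance ratio itself does not depend on the number of subjects.

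**Step 1: variances.** With the same standard deviation s at both visits:

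- change score: 2(1 − rho)s²
- ANCOVA residual: (1 − rho²)s²
- ratio: (1 − rho²) / [2(1 − rho)] = (1 + rho)/2

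If the standard deviations differ (s0 at baseline, s1 at 3 months), the change-score variance minus the ANCOVA variance is s0² − 2·rho·s0·s1 + rho²·s1² = (s0 − rho·s1)². This is never negative, so adjustment does not lose precision apart from degrees of freedom.

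**Step 2: anchor.** With 26 per arm, 80% power needs a difference of (1.960 + 0.842) × √(2/26) = 0.78 standard deviations of the analysed variable (0.79 with the t distribution).

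**Step 3: power after adjustment.** Keep that difference fixed. Power is then Φ(2.802/√ratio − 1.960). For rho = 0.5: 2.802/√0.75 = 3.235, and Φ(1.275) = 0.899.

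| Assumed rho | Variance ratio | Power, change score | Power, ANCOVA | CI narrower by | 52 subjects act like (52/ratio) |
|---|---|---|---|---|---|
| 0.5 | 0.75 | 80% | 89.9% | 13% | 69 |
| 0.7 | 0.85 | 80% | 86.0% | 8% | 61 |
| 0.8 | 0.90 | 80% | 84.0% | 5% | 58 |
| 0.9 | 0.95 | 80% | 82.0% | 2.5% | 55 |
| 0.95 | 0.975 | 80% | 81.0% | 1.3% | 53 |

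**Step 4: chance imbalance.** The difference in baseline means has standard deviation √(2/26) = 0.277s. Given an imbalance of that size, the expected change-score difference shifts by (1 − rho) × 0.277s: 0.139s at rho = 0.5 and 0.028s at rho = 0.9. This is the same loss as in Step 1, seen in a single trial, and is not an extra one.

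**Step 5: cost of the covariates.** In a simulation of 20,000 trials per rho, with the stratum given no prognostic effect, the variance ratio for baseline plus stratum was 0.76, 0.87 and 0.97 at rho = 0.5, 0.7 and 0.9. The ideal values are 0.75, 0.85 and 0.95, so an uninformative stratum costs very little. Residual degrees of freedom fall from 50 to 48.

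**Step 6: the conditional step.** In the same simulation under the null, the 0.05 to 0.25 window was entered in about 20% of trials. If the adjusted result were then accepted as the test, with baseline and stratum as covariates, the type I error was 6.0% to 6.7% instead of 5%. The article does not say that the step would be used in this way.

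**The case against.** The strongest reply is that the article defines an outcome variable and not a between-arm model. The t-test appears in sentences about predictors, and the decision rule neither includes nor excludes covariates. A condensed article may leave the model to a fuller plan. This stands in part: the absence of a covariate list alone would be no finding. But section 4.3 does fix the change score, offers no other test for the comparison of arms, and makes any adjustment depend on a p-value.

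Four stronger readings are tempting, and the article does not support them:

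- **The change score biases the result.** Under randomisation it is unbiased. A chance imbalance shifts the estimate only conditionally on that imbalance.
- **Baseline is ignored.** It enters by subtraction; it is only not a covariate.
- **Omitting the stratum makes the standard error wrong.** That holds only if stenosis is prognostic for the outcome, and then the unadjusted test tends to be conservative. The article gives no evidence on this either way.
- **There are two rival primary tests.** The two wordings of the null coincide in expectation under randomisation, because expected baselines are equal. The primary endpoint in the Abstract, the alternative hypothesis and the outcome definition all refer to change. The second wording is loose and should be tidied.

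It is also fair to say that a high correlation between scans 3 months apart cannot be excluded. The gain would then be slight, in what the article describes as a feasibility study.

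**Conclusion.** The point holds as a matter of efficiency and prespecification, not of validity. The plan's change score is a legitimate estimator, but a less precise one than ANCOVA for any correlation below 1 when the variances at the two visits are equal. From a starting power of 80%, the gain ranges from about 10 percentage points at rho = 0.5 to about 1 point at rho = 0.95. The article gives no basis for choosing within that range, and the 80% is only a reference point.

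Including the stratum brings the analysis into line with the allocation; it adds precision only if stenosis is prognostic. The conditional multivariate step is no substitute, because it leaves the estimate unadjusted whenever p falls outside its window and names no covariates.

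ANCOVA alone does not make the outcome well defined. The formula in section 4.3 subtracts baseline maximal uptake from end-of-study standard uptake value and target-to-background ratio. The metric must be the same at both visits before either analysis can be run. The change is worth making because it is almost free.

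**What to change.** 1. Prespecify one primary analysis: a linear model of 3-month uptake on arm, baseline uptake and stenosis stratum (25–50% / > 50%).
2. Name one uptake metric and use it at both visits.
3. Report the adjusted difference between arms with its 95% confidence interval and two-sided 5% test.
4. State the null once, for that difference. With the same-metric baseline in the model, the arm coefficient is identical whether the response is the 3-month value or the change, so the two wordings no longer matter.
5. Remove the p-value-triggered multivariate step from the treatment comparison. A search for predictors can remain as a separate exploratory analysis.
6. Use the analogous model, each with its own baseline, for the continuous secondary outcomes: CAC score, ultrasound measures, MRI volumes and normalized wall index, and dp-ucMGP, transformed where needed. Fibrous cap status is categorical and needs a different method.

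The cost is a change of wording in the analysis plan and two degrees of freedom. No new data are required.
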